## Abstract

**Background:**

Bilberries from Sweden, rich in polyphenols, have shown cholesterol-lowering effects in small studies, and the cholesterol-lowering properties of oats, with abundant beta-glucans and potentially bioactive phytochemicals, are well established. Both may provide cardiometabolic benefits following acute myocardial infarction (AMI), but large studies of adequate statistical power and appropriate duration are needed to confirm clinically relevant treatment effects. No previous study has evaluated the potential additive or synergistic effects of bilberry combined with oats on cardiometabolic risk factors. Our primary objective is to assess cardioprotective effects of diet supplementation with dried bilberry or with bioprocessed oat bran, with a secondary explorative objective of assessing their combination, compared with a neutral isocaloric reference supplement, initiated within 5 days following percutaneous coronary intervention (PCI) for AMI.

**Methods:**

The effects of *Bi*lberry and *O*at intake on lipids, inflammation and exercise capacity after *A*cute *M*yocardial *I*nfarction (BIOAMI) trial is a double-blind, randomized, placebo-controlled clinical trial. A total of 900 patients will be randomized post-PCI to one of four dietary intervention arms. After randomization, subjects will receive beverages with bilberry powder (active), beverages with high-fiber bioprocessed oat bran (active), beverages with bilberry and oats combined (active), or reference beverages containing no active bilberry or active oats, for consumption twice daily during a 3-month intervention. The primary endpoint is the difference in LDL cholesterol change between the intervention groups after 3 months. The major secondary endpoint is exercise capacity at 3 months. Other secondary endpoints include plasma concentrations of biochemical markers of inflammation, metabolomics, and gut microbiota composition after 3 months.

**Discussion:**

Controlling hyperlipidemia and inflammation is critical to preventing new cardiovascular events, but novel pharmacological treatments for these conditions are expensive and associated with negative side effects. If bilberry and/or oat, in addition to standard medical therapy, can lower LDL cholesterol and inflammation more than standard therapy alone, this could be a cost-effective and safe dietary strategy for secondary prevention after AMI.

**Trial registration:**

ClinicalTrials.gov NCT03620266. Registered on August 8, 2018.

**Supplementary Information:**

The online version contains supplementary material available at 10.1186/s13063-021-05287-5.

## Background

Cardiovascular disease (CVD) is a leading cause of death and disability globally. Dyslipidemia is a major modifiable risk factor for the development of atherosclerotic plaques [1]. Systemic inflammation also plays a central role in the atherosclerotic process from initiation through progression and rupture of plaques [2, 3]. Observational studies suggest that the risk of acute myocardial infarction (AMI) in persons with hyperlipidemia is three times that of the population with normal lipid status. A reduction in serum cholesterol is strongly associated with a reduction in CVD risk [4, 5]. Secondary prevention after AMI has improved in recent decades, but readmissions and death following AMI remain important challenges. Although new lipid-lowering medications are effective in reducing low-density lipoprotein (LDL) cholesterol levels, clinical guidelines advocate addition of non-statin agents [6], but their cost/efficacy is debatable even in high-risk patients [7].

From a public health perspective, lifestyle modification, including dietary changes, is considered a first step in controlling and treating CVD risk factors [8]. However, patients at highest risk of premature death, AMI, and re-hospitalization are those with known CVD [9]. Consequently, international guidelines recommend secondary prevention strategies to reduce subsequent cardiovascular risk, such as evidence-based pharmacological therapy and adherence to diet and physical activity regimens [10]. Studies have shown positive effects on cardiovascular risk factors of a Nordic diet, in which berries and oats are important elements [11, 12]. However, food supplement clinical trials that include subjects with overt disease are scarce, and there is a need for well-planned and well-executed controlled intervention studies of sufficient size and duration to provide a firm evidence base for dietary guidance in both healthy individuals and those suffering from heart disease [13–15].

A meta-analysis of more than 50 clinical trials concluded that oats can lower LDL cholesterol by 5–8% [16], and subsequent data suggest other anti-atherogenic properties of oats, including reducing inflammation and oxidative stress [17]. Recent studies indicate that bilberries from Sweden, rich in polyphenols and anthocyanins, may have direct or indirect positive effects on cardiovascular risk factors [13, 18, 19]. It has been suggested that consumption of the anthocyanins present in bilberries may reduce risk of death from CVD [20–22], have beneficial effects on platelet function, increase high-density lipoprotein (HDL) cholesterol [23, 24], and improve exercise tolerance [25, 26]. The mechanisms of action of berries are likely to be different from those of oats, potentially providing additive or synergistic beneficial effects. We recently conducted a small open-label randomized clinical trial of bilberry supplementation in patients post-AMI receiving high-dose statin treatment and found significant beneficial effects on lipid profile and exercise capacity in patients receiving bilberry supplementation [27]. We are proceeding to conduct a large, randomized, placebo-controlled clinical trial to assess clinical impact.

## Methods

### Study design, hypotheses, and primary and secondary endpoints

The effects of *Bi*lberry and *O*at intake on lipids, inflammation and exercise capacity after *A*cute *M*yocardial *I*nfarction (BIOAMI) trial is a prospective, randomized, double-blind, placebo-controlled multicenter trial in patients post-AMI. The primary objective is to assess differences in LDL cholesterol change among treatments after 3 months of a diet supplemented with a beverage containing either dried bilberry or bioprocessed oat bran compared with a neutral isocaloric reference drink, initiated within 5 days following percutaneous coronary intervention (PCI) for AMI. A secondary objective is to assess the combination of bilberries and oats compared with the reference drink. We hypothesize that standard medical therapy supplemented with either dried bilberries or bioprocessed oat bran post-AMI will show a more beneficial effect on LDL cholesterol than medical therapy alone after 3 months. Additional secondary objectives are to determine effects on exercise capacity, biomarkers of inflammation and other biochemical markers, resting heart rate, blood pressure, and left ventricular systolic function (Table 1). We will also employ untargeted metabolomics to exploratively assess alterations in endogenous and exposome-related metabolites and effects on gut microbiota composition and activity. These exploratory analyses will allow us to investigate the extent to which gut microbiota composition and activity differs between responders and non-responders to the interventions. At 1-year following randomization, we will exploratively assess clinical endpoints in all randomized patients using data from the Swedish Coronary Angiography and Angioplasty Registry (SCAAR) with respect to death, new AMI, and new unplanned revascularization.

**Table 1 Tab1:** Primary and secondary endpoints

Primary endpoint • LDL-C cholesterol Major secondary endpoint • Symptom-limited bicycle ergometer test (Watts and estimated VO_2_max) Other secondary endpoints • Dynamic unilateral heel-lift and unilateral shoulder-flexion tests (*n*) • Self-reported activity level (levels 1–6, days/week) • Fasting lipid levels (TC, HDL-C, TGA, small dense LDL-C, apo A, apo B, Lp(a), oxidized LDL) • Fasting insulin, c-peptide, creatinine, glucose, cystatin C • HbA1c, hs-CRP, NT-proBNP, troponin-I, IL-6 • Resting heart rate and blood pressure • Left ventricular systolic function • Untargeted plasma metabolome • Gut microbiota composition	

### Study population and patient selection

Subjects in this multicenter study will be recruited from among patients referred to Sahlgrenska University Hospital Gothenburg, Umeå University Hospital, Lund University Hospital, Västerås general hospital, Karlstad general hospital, and Örebro University Hospital for coronary angiography/PCI due to ST-segment elevation myocardial infarction (STEMI) or non-ST-segment elevation myocardial infarction (NSTEMI). STEMI is defined as chest pain suggestive of myocardial ischemia for at least 30 min prior to hospital admission with time from onset of symptoms less than 24 h, an ECG with new ST-segment elevation in two or more contiguous leads of ≥ 0.2 mV in leads V2–V3 and/or ≥ 0.1 mV in other leads, or a probable new-onset left bundle branch block. NSTEMI is defined as a combination of onset of symptoms such as central chest pain or aggravated angina pectoris, with or without ECG changes, with ST-segment depression or an inverted T-wave and rise and/or fall of troponin-T or troponin-I above the established margin of an AMI. Study inclusion and exclusion criteria are defined in Table 2.

**Table 2 Tab2:** Inclusion and exclusion criteria

Inclusion criteria • STEMI or NSTEMI • Completed coronary angiography/PCI • Male and female subjects ≥ 18 years • Allocated to atorvastatin at a daily dose of 80 mg • Written informed consent Exclusion criteria • Emergency coronary artery bypass grafting • < 18 years of age • LDL cholesterol < 2.0 mmol/L • Daily intake or the intent to initiate daily intake of bilberry in any form or daily intake of > 15 g of oatmeal or equivalent • Previous randomization in the BIOAMI trial • Inability to provide informed consent	

### Randomization

Potential trial participants will receive written information of the study, and they will receive oral information by medical doctors participating in the study. Informed consent shall be obtained by a Good Clinical Practice-qualified medical doctor or research nurse participating in the study. After providing written informed consent, patients who fulfill inclusion criteria and with no exclusion criteria will be randomized according to a computer-generated random-number sequence. Block randomization is performed in a 1:1:1:1 fashion stratified by study center (Fig. 1). The study will be using SMART-TRIAL® (MEDEI ApS, Aalborg, Denmark), a combined password-protected web-based randomization module and eCRF, in each participating hospital, in order to keep the data management and the statistician blind against the study condition as long as the data bank is open. The randomization list remains with SMART-TRIAL for the whole duration of the study. Thus, randomization will be conducted without any influence of the principal investigators, raters or therapists. Patients, investigators, and all medical staff will be blinded to allocation.

**Fig. 1 Fig1:**
[figure not shown]
Flowchart of study design. AMI, acute myocardial infarction; PCI, percutaneous coronary intervention

All randomized patients will receive standard medical and interventional treatment for AMI, including atorvastatin at a daily dose of 80 mg. The regimen for enrolment, data collection, interventions, and assessments of the trial is further shown in Fig. 2.

**Fig. 2 Fig2:**
[figure not shown]
SPIRIT figure of the trial procedure including enrolment, data collection, intervention, and assessments

### Dietary intervention

Subjects will be randomized to one of the four dietary intervention arms initiated within 5 days post-PCI and continued for 3 months. After randomization, subjects will receive beverages with bilberry powder (active), beverages with high-fiber bioprocessed oat bran (active), beverages with bilberry and oats combined (active), or reference beverages containing no active bilberry or active oats, for consumption twice daily (160 kcal/day).

The beverages will be balanced to ensure isocaloric conditions. Intake twice a day is considered appropriate given the relatively short elimination half-life of anthocyanins which are believed to be important for the hypothesized effect from bilberries. The study products are under development by food scientists at Glucanova (Lund, Sweden) in collaboration with Chalmers University of Technology, Gothenburg, Sweden. Dried bilberry powder is provided by Immun (Skellefteå, Sweden). The oat bran will be bioprocessed to enable production of a palatable oat bran drink. The daily dose of oat bran will be 50 g, providing approximately 9.5 g dietary fiber of which 5 g beta-glucans, as well as abundant potentially bioactive phytochemicals, such as the oat-specific polyphenolic avenanthramides. The daily dose of the active bilberry product will contain 40 g dried bilberry powder, equal to approximately 480 g of fresh berries. Bilberry powder contains multiple anthocyanins and other polyphenols [27], the levels of the specific batches used in the present study will be analyzed in the intervention products and reported at a later date. The quantity of bioprocessed oat bran and bilberry powder in the combined study product will be 50% that of the separate supplements. The four study products are designed with similar texture and to look and taste as if they contain both bilberries and liquid oats, to enable double blinding. The reference product is based on starch, collagen, corn oil, sucrose, and citric acid. Small amounts of starch, collagen and corn oil were also added to the dried bilberry drink and the bilberry + oats drink to ensure isocaloric conditions as well as similar nutrient profiles and sensory properties (Table 3). Subjects will be instructed not to consume foods containing bilberry other than the intervention products, and no more than 15 g of oatmeal, or the equivalent, per day, during the intervention. Dietary advice according to routine treatment after AMI will be given to all study subjects.

**Table 3 Tab3:** Nutritional content of study products

Nutrition (g/100g)	Dried bilberry drink	Bioprocessed oat bran drink	Bilberry + oat bran drink	Reference drink
Energy (kcal/100g)	32.1	32.7	32.0	32.3
Fat	0.6	0.9	0.9	0.7
- Of which saturated fat	0.1	0.2	0.1	0.1
Protein	0.9	2.0	1.4	1.3
Carbohydrate	4.8	3.3	3.7	5.3
- Of which sugars	3.0	2.0	2.5	2.2
Dietary fiber	1.8	1.9	1.9	0.0
- Of which β-glucan	0.0	1.0	0.5	0.0
Salt	0.06	0.05	0.00	0.02

### Examinations and blood tests

Subjects will be assessed at baseline, as inpatients, and at 3-month follow-up as outpatients. Examinations and samples will be collected as follows.

#### Blood and fecal samples

Venous blood samples will be collected at baseline and during intervention week 12. The blood samples will be centrifuged immediately and stored at – 80 °C pending further analyses. Fasting lipid profile [low-density lipoprotein cholesterol (LDL-C); total cholesterol (TC); high-density lipoprotein cholesterol (HDL-C); triglycerides (TG); small dense low-density lipoprotein (sdLDL); oxidized LDL; apolipoprotein A (apo A); apolipoprotein B (apo B); lipoprotein(a) (lp[a]); inflammatory markers high-sensitivity C-reactive protein (hs-CRP) and interleukin 6 (IL-6); fasting glucose; insulin; creatinine; cystatin C, C-peptide; glycosylated hemoglobin (HbA1c); and the heart function markers troponin-I and N-terminal pro b-type natriuretic peptide (NT-proBNP)] will be analyzed.

Analysis of blood samples will be conducted to assess diet compliance based on the presumption that the concentrations of phenolic acid derivatives will be higher in the bilberry group and avenanthramides and/or avenocosides higher in the oat and combined bilberry/oat groups compared to the reference group [27]. Phenolic acid derivative components associated with bilberry consumption [28] and avenanthramides associated with oats will be analyzed by a validated method combining liquid chromatography with mass spectrometry [29, 30].

Fecal samples will be collected at baseline and during intervention week 12. All samples will be processed and stored for metabolomics and microbiome analyses using a fecal collection kit. For metabolomics and microbiome testing, plasma and fecal samples will be collected pre- and post-intervention and stored for untargeted metabolomics and microbiota analysis at Chalmers University in Gothenburg, Sweden. Plasma samples will be processed and analyzed in four modes (reverse phase/HILIC chromatography in positive/negative ionization modes, respectively) on an LC-QTOF-MS instrument according to an established protocol [31, 32]. This will ensure the most comprehensive collection of endogenous and exposome-related metabolites. Gut microbiome will be analyzed by sequencing 16S rRNA amplicons using Illumina MiSeq. Data analysis strategies such as partial least squares (PLS) and random forest will be used to identify metabolites and microbiota that differ with treatment, as well as to detect metabolite and bacterial composition that may be related to high versus low responders to LDL-lowering treatment [33]. All analyses will be performed blinded, without knowledge of clinical diagnosis or randomization.

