### Sample size calculation, data management, and statistical analysis

To the best of our knowledge, no previous intervention study of bilberry/oats with LDL cholesterol as an endpoint in AMI patients has been conducted. Required sample size is calculated on the basis of bilberry-specific interventions from four smaller randomized studies in at-risk populations [18], from our pilot study [27], and from the IMPROVE-IT trial [44], which found a clinically relevant LDL cholesterol-lowering effect of − 0.4 mmol/L when adding treatment with a non-statin agent to standard statin lipid-lowering therapy after AMI. We calculated that 189 subjects would be needed in each study arm to provide 90% statistical power to detect a 0.4 mmol/L or greater reduction in LDL cholesterol in the bilberry or the oat treatment group compared to the reference, with a standard deviation of 1.1 mmol/L and a Bonferroni corrected overall 5% two-sided significance (Statistical Solutions Ltd, Cork, Ireland). The correction is due to two primary hypotheses, (1) bilberry group vs. reference and (2) oat group vs. reference. The same number of participants will be enrolled in the combined bilberry and oat treatment group, for a total of 756 patients in the study. In order to allow for an anticipated dropout rate of ~ 15%, we plan to include 900 patients, 225 in each study arm.

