In contrast to previous smaller studies in at-risk populations, the proposed study is powered to evaluate clinically relevant effects on LDL cholesterol in patients following overt AMI. In addition, we will use untargeted metabolomics to detect potential biomarkers of responders and non-responders to the interventions and characterize gut microbiome/diet interactions, as well as to investigate how metabolic networks are affected by the interventions.

All AMI patients in our pilot study received statin therapy. Bilberry administration was initiated within 72 h of PCI during a vulnerable and critical clinical phase [55, 56]. Despite statin treatment, we found significant correlation of LDL cholesterol and oxidized LDL with blood levels of anthocyanins after an 8-week intervention, indicating a possible dose-response relationship of anthocyanins in bilberries with cholesterol levels. The lipid-lowering effect of bilberry could be partly explained by the high anthocyanin content [57]. Oxidized LDL is associated with all stages of atherosclerosis and with co-morbidities linked to CVD, such as diabetes mellitus, hypertension, and obesity [58]. We speculate that both bilberries and oats could play a role in supplementing medical therapy, but probably through different mechanisms, showing potential for cumulative or synergistic beneficial effects. Both bilberries and oats are natural foods that have shown potential for CVD prevention when provided separately, but their combined effects have not been studied in clinical trials nor have effects of bilberries or oats been studied in large populations with overt disease, as in this trial with 900 AMI patients. A synergistic effect of oats and bilberries could suggest development of novel cholesterol-lowering functional foods as a potential cost-effective and safe dietary strategy for reduction of cardiac risk after AMI.

In designing the intervention drinks, we faced a challenge regarding calorie intake. In order to balance the four intervention drinks calorie-wise and to avoid high contents of sucrose and starch content in the reference product, we designed the combined bilberry/oat drink to contain half the quantity of bilberry and oats in the separate drinks. Our study therefore does not fulfill 2 × 2 factorial design criteria, and this limits our ability to investigate possible interactions between bilberries and oats without making assumptions about the linear dose-response relationship.

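### The exploratory omics analysis frames LDL response as high versus low responders without a reason or a cut; a continuous, baseline-adjusted LDL change would keep information that any grouping loses

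*Protocol article*

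**What the plan says.** The protocol article puts the response question as a contrast of two groups in three places.

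- Methods, Blood and fecal samples: the supervised methods are meant to "detect metabolite and bacterial composition that may be related to high versus low responders to LDL-lowering treatment".
- Methods, Study design, hypotheses, and primary and secondary endpoints: the aim is to "investigate the extent to which gut microbiota composition and activity differs between responders and non-responders to the interventions". The same sentence labels these analyses exploratory.
- Discussion: "we will use untargeted metabolomics to detect potential biomarkers of responders and non-responders to the interventions".

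The tools are named in Blood and fecal samples: "Data analysis strategies such as partial least squares (PLS) and random forest will be used to identify metabolites and microbiota that differ with treatment". The section on sample size, data management and statistical analysis repeats PLS and random forest and describes the omics work as explorative and mainly multivariate.

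That same section analyses the primary outcome, LDL change, by linear regression adjusted for the baseline value, so there it stays continuous. Nowhere does the article describe LDL change as a continuous outcome for the omics work. It also gives no responder definition, threshold or group share, and does not say whether patients in the middle of the distribution are kept.

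**The concern.** One variable is handled in two ways, and no reason is offered for the coarser one. LDL change has no natural boundary between response and non-response, and the article proposes none. Once it is grouped, patients just either side of the boundary count as opposites, while patients far apart on the same side count as equal.

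The cost falls on the ability to find markers of response. Untargeted metabolomics and 16S sequencing screen very many features, so any per-feature threshold is likely to be strict. At a strict threshold, lost information costs the most power for markers of moderate strength. Both named tools accept a continuous outcome, so the grouping is not forced by the method.

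**Working it through.** **Inputs.** The article gives no sample size, significance level, effect size or power for the responder analysis. Its only design figure is for the primary comparison: "189 subjects would be needed in each study arm to provide 90% statistical power" to "detect a 0.4 mmol/L or greater reduction in LDL cholesterol", with SD 1.1 mmol/L and 5% two-sided, Bonferroni-corrected for two hypotheses (2.5% each).

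**Step 1: the plan's own figure.** n per arm = 2 × (1.1/0.4)² × (2.2414 + 1.2816)² = 15.125 × 12.411 = 187.7, so 188 by the normal approximation. With the noncentral t distribution it is 189 (power 0.9000). The stated 189 is reproduced. It is borrowed below only as an illustrative size for an analysis within one arm; the article does not say that the responder analysis is run per arm.

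**Step 2: information kept after one cut.** For a normal response cut so that a share q lies on one side, the efficiency relative to the continuous response is φ(z_q)² / [q(1 − q)].

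- Median: 0.3989² / 0.25 = 0.637 (= 2/π), a loss of 36.3%.
- One third against two thirds: 0.3636² / 0.2222 = 0.595, a loss of 40.5%.
- One quarter against three quarters: 0.539, a loss of 46.1%.

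The median is the least costly single cut, so 36% is the minimum loss under this reading.

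**Step 3: information kept with extreme groups.** If the top and bottom shares q are compared and the middle is dropped, the efficiency is 2q × (φ(z_q)/q)². For thirds this is 0.6667 × 1.0908² = 0.793, a loss of about 21%. For quarters it is 0.808, a loss of about 19%.

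**Step 4: what this means for power.** The assumptions are a bivariate normal marker and response, n = 189, one marker tested at a time, and correlations of 0.20 to 0.30. None of these comes from the article. Simulated power (6,000 data sets per setting):

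| Correlation | Two-sided alpha | Continuous | Median cut | Top-third cut | Loss (points) |
|---|---|---|---|---|---|
| 0.20 | 0.05 | 79% | 60% | 55% | 19 to 24 |
| 0.25 | 0.05 | 94% | 79% | 77% | 15 to 17 |
| 0.30 | 0.05 | 99% | 92% | 90% | 7 to 9 |
| 0.20 | 0.001 | 29% | 14% | 11% | 15 to 18 |
| 0.25 | 0.001 | 58% | 29% | 27% | 29 to 31 |
| 0.30 | 0.001 | 82% | 51% | 46% | 31 to 36 |

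**Step 5: cross-check by formula.** Power ≈ Φ(√efficiency × atanh(r) × √(n − 3) − z_alpha). For r = 0.25, atanh(r) × √186 = 3.483.

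- At 0.05, continuous: Φ(3.483 − 1.960) = 0.94. Median cut: Φ(0.798 × 3.483 − 1.960) = 0.79.
- At 0.001, continuous: Φ(3.483 − 3.291) = 0.58. Median cut: Φ(2.779 − 3.291) = 0.30.

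These agree with the simulation to within about two points.

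**Step 6: extreme thirds.** In a separate simulation with n = 189 and about 80% power on the continuous response at two-sided 0.05, power was 79.9% continuous, 60.2% after a median split and 71.3% with extreme thirds. The extreme-thirds reading therefore costs about 9 points there, against about 20 for the median split.

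**The case against.** The strongest reply is that the article fixes no cut and no classification mode. It names PLS, not its discriminant form, introduces the methods as examples, and does not rule out a regression on LDL change followed by a description of high and low responders. The coding of an exploratory response variable is commonly left to the full protocol or analysis plan, neither of which is shown.

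Much of this stands. The missing cut point is not itself a fault. A reader might infer that a dichotomy is settled and that over a third of the information, with a definite number of power points, will be lost. The article does not support that: it gives no cut, mode, significance level, sample size or effect for this analysis. A loss above one third holds only for a single cut with every patient kept; comparing extreme groups loses much less.

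Two further limits also stand. The planned methods are multivariate, so single-marker power figures do not measure their performance. The responder contrast is also not listed among the endpoints in Table 1.

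What the reply does not remove is the contrast itself. It is stated three times, a continuous alternative is never mentioned for the omics work, and no reason for grouping is given. Leaving the threshold to another document does not supply that reason.

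**Conclusion.** The point holds as a low-severity, conditional improvement. The two-group framing is a stated choice that the article does not justify, and it departs from the continuous treatment of the same variable in the primary analysis.

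The size depends on how the groups are formed: a loss of at least 36% of the information for one cut, and about 21% for extreme thirds, assuming an approximately normal response. For a median or top-third cut, the illustrative power loss is roughly 7 to 24 points at two-sided 0.05 and 15 to 36 points at 0.001. That range rests on assumed correlations of 0.20 to 0.30, 189 patients and single-marker tests, so no single figure can be attributed to this trial. If the full plan already models LDL change as continuous, only the article's wording needs to change.

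The consequence is confined to an exploratory analysis.

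**What to change.** In the three places quoted (Study design, hypotheses, and primary and secondary endpoints; Blood and fecal samples; Discussion), name LDL change as a continuous outcome, adjusted for baseline LDL, as the main response variable for the metabolome and microbiota analyses. Fit it with PLS regression and random-forest regression. Keep high and low groups for display or as a secondary description; if they are used for inference, fix and justify the cut in advance.

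The cost is a change of wording. The samples, patients and software stay the same, because both named tools have a regression form.
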